### Primary outcomes

As recommended by the Society for Research on Nicotine and Tobacco expert workgroup [37], the primary outcome is defined as self-reported 6-month prolonged abstinence (with no relapse, i.e. 7+ days of prolonged smoking) at the 7-month follow-up, allowing participants up to 1 month to stop smoking.

### Secondary outcomes

Secondary outcomes assessed at 7-month follow-up will include:

#### Smoking

Biochemically verified abstinence from smoking (for participants reporting prolonged abstinence at the 7-month follow-up, and no smoking in the last week). Measured via breath carbon monoxide monitor or salivary cotinine test.Length of quit attempts (defined as stopping smoking for a period of 24 h or more). Past quit attempts are predictive of future attempts [38].Nicotine dependence: assessed using the two item Heaviness of Smoking Index (HSI [39]). It uses a six-point scale calculated from the number of cigarettes smoked per day (1–10, 11–20, 21–30, 31+) and the time to first cigarette after waking (< 5, 6–30, 31–60 and 61+ min). Nicotine dependence is then categorized into a three-category variable: low (0–1), medium (2–4) and high (5–6).Daily consumption: cigarettes per day (CPD) as measured by item 1 of the HSI; ‘How many cigarettes do you typically smoke per day?’ HSI and CPD are strong predictors of quitting behaviour [40].

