### Primary hypotheses

1a) The proportion of smokers and recent quitters receiving anti-cancer therapy who achieve self-reported 6-month prolonged abstinence from smoking will be higher post-intervention compared to pre-intervention (14% vs. 7%).

1b) Biochemically verified 7-day point-prevalence abstinence from smoking at 7 months post-recruitment will be higher after the intervention phase than at the baseline phase (25% vs. 15%).

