### Participant timeline

This protocol is presented in accordance with the 2013 Standard Protocol Items: Recommendations for Interventional Trials (SPIRIT) Statement (see Supplementary Material). The schedule of enrolment, interventions, and assessments is summarized in Table 1.

**Table 1 Tab1:** Stepwise procedures

Week	0	1	…	31	
Contact	*1*	*2*		*3*	
Enrolment					
Screening	X				
Informed consent	X				
Baseline assessment					
Computer-assisted telephone interview		X			
Follow-up assessment					
Computer-assisted telephone interview				X	
Biochemical verification of abstinence^a^ (breath carbon monoxide or salivary cotinine test)				X	
Post study period					
Medical record audit					X
Quitline data extraction^b^					X

^a^For reported abstainers

^b^For participants who report using the Quitline service

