**Fig. 2 Fig2:**
[figure not shown]
Cessation care model

*Ask*: Assess and record smoking status (current smoker or recent quitter);

*Advise*: Give a personalised description of the specific benefits of smoking abstinence during and after treatment; endorse use of evidence-based support (telephone counselling and pharmacotherapy);

*Act*/*Help*: Offer referral to Quitline or other local cessation support service (including education around the benefits of Quitline); prescribe, provide or advise on pharmacotherapy options (nicotine replacement therapy (NRT) or varenicline) which are safe during treatment; and monitor progress. The above components of the cessation care model are the staff behaviours that our implementation intervention (described below) aims to target. A description of how these will be measured is provided in secondary outcomes (provision of smoking cessation care) and Table 2.

**Table 2 Tab2:** Assessment schedule

	Baseline	7 months	
^a, b^Demographic and disease characteristics	X		
^a^Cancer site	X		
^a, b^Cancer treatment	X	X	
^a^Time since diagnosis	X		
^a^6 month prolonged abstinence (primary outcome)		X	
Saliva sample or CO breath test (those reporting abstinence)		X	
^a^Length of quit attempts		X	
^a^Heaviness of smoking index (including CPD)	X	X	
^a^Motivation to Quit	X	X	
^a^Self-efficacy to quit	X	X	
^a^Perceived benefit of quitting	X	X	
^a^Other smokers in household	X	X	
^a^Perceived social support	X		
^a^Risk perceptions	X	X	
^a^Use of pharmacotherapy	X	X	
Delivery of cessation support			
^a, b^Advice to quit	X	X	
^a, b, c^Proactive referral to Quitline	X	X	
^a, b^Prescription or provision of pharmacotherapy (including perceived acceptability)	X	X	
Mental health			
^a^PHQ-4 (+ 2 items from the PHQ to assess panic attack history)	X	X	
Substance use			
^a^Alcohol (AUDIT-C)	X	X	
^a^Cannabis use with tobacco q	X	X	
^a^Cannabis (First question of CUDIT)	X	X	
Quality of life			
^a^FACT–G7	X	X	
Financial effects			
^a^Financial stress scale	X	X	
^a^Financial distress thermometer	X	X	
Patient process measures			
^a^Patient recall of advice to quit	X	X	
^a^Patient recall of referral	X	X	
^a^Patient recall of pharmacotherapy prescription or provision	X	X	
^a^Attitudes and acceptability of receiving cessation support	X	X	
Cost data			
^g^Resource development, training/meetings, equipment/consumables		X	
	Baseline	Intervention (12 months duration)	Post-intervention (9–12 months duration depending on step)
Staff Process measures			

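### Hypothesis 1b's verified 7-day abstinence of 25% vs 15% does not fit an outcome definition that tests only prolonged abstainers, put at 14% vs 7% in hypothesis 1a

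*Protocol article*

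**What the plan says.** Four places in the protocol article bear on this point.

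- **Primary hypotheses, 1a.** The proportion who "achieve self-reported 6-month prolonged abstinence from smoking will be higher post-intervention compared to pre-intervention (14% vs. 7"%).
- **Primary hypotheses, 1b.** The outcome is "Biochemically verified 7-day point-prevalence abstinence from smoking at 7 months post-recruitment", and it "will be higher after the intervention phase than at the baseline phase (25% vs. 15"%).
- **Secondary outcomes, Smoking.** The only definition of the verified outcome is "Biochemically verified abstinence from smoking (for participants reporting prolonged abstinence at the 7-month follow-up, and no smoking in the last week"), measured by breath carbon monoxide or salivary cotinine.
- **Tables 1 and 2.** The footnote to Table 1 gives the test population as "For reported abstainers". Table 2 lists "Saliva sample or CO breath test (those reporting abstinence"). Neither says which kind of abstinence is meant.

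The Primary outcomes section defines prolonged abstinence as "self-reported 6-month prolonged abstinence (with no relapse, i.e. 7+ days of prolonged smoking) at the 7-month follow-up", with up to one month allowed for stopping.

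**The concern.** Seven-day point prevalence and six-month prolonged abstinence are different states. A patient who stopped in month 3, or who relapsed and stopped again in month 5, may have been smoke-free for the past week at the 7-month interview without meeting the prolonged definition. Hypothesis 1b covers such patients; the Smoking section does not call for testing them.

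The testing rule is narrower even than the primary outcome. The primary definition counts only 7 or more days of smoking as relapse, so someone with a short lapse in the final week can be a prolonged abstainer and still fail the no-smoking-last-week condition.

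What is at stake is the trial's only objective smoking outcome. The protocol itself warns that people with cancer may report abstinence while still smoking, and its primary outcome rests on self-report. Who is tested is a data-collection rule: no analysis plan can restore a breath or saliva sample that was not taken at month 7.

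**Working it through.** **Inputs.** Prolonged abstinence 14% and 7% (hypothesis 1a); verified 7-day abstinence 25% and 15% (hypothesis 1b); testing rule (Smoking section); 40 recruits per site per 6 months, 3 years, nine sites, intra-cluster correlation 0.01, cluster autocorrelation 0, alpha 0.05 (Sample size); intervention starts at 6, 13 and 19 months (Implementation of Care to Quit); 6-month offset of the intervention indicator (Statistical methods).

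**Step 1: reproduce the plan's own figures.** Sample size: 40 × 6 × 9 = 2160, as stated.

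For power, assume four equal phases of 60 per site (2160/9/4), three sites crossing per step, two-sided alpha and a normal approximation on the risk-difference scale. The layout is an assumption, because Fig. 1 is not shown.

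- Average binomial variance = (0.07 × 0.93 + 0.14 × 0.86)/2 = 0.09275.
- Variance of a site-phase mean = 0.09275 × (0.01 + 0.99/60) = 0.002458.
- With autocorrelation 0, phases contribute separately. Information is the sum of treated × control / 9 over phases: 0 + 18/9 + 18/9 + 0 = 4.
- Standard error = √(0.002458/4) = 0.0248.
- Power = Φ(0.07/0.0248 − 1.96) = 0.806, matching the stated value of about 80%.

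**Step 2: subset bound.** Under the Smoking section,

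P(verified) = P(prolonged and no smoking last week and test passed) ≤ P(prolonged).

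| | Ceiling, from 1a | Hypothesised, 1b | Ratio |
|---|---|---|---|
| Intervention | 14% | 25% | 25/14 = 1.79 |
| Control | 7% | 15% | 15/7 = 2.14 |

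Per 1000 participants, 250 and 150 verified abstainers would have to come from 140 and 70 prolonged abstainers. This step does not depend on the layout in step 1.

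**Step 3: who falls outside the rule.** If 1a and 1b both hold, at least 25 − 14 = 11 of every 25 expected verified abstainers (44%) in the intervention condition are not called for testing, and at least 15 − 7 = 8 of every 15 (53%) in control.

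**Step 4: does another denominator help?** To turn 14% into 25% and 7% into 15% with every test passed, the denominators would have to be 14/25 = 56% and 7/15 = 47% of participants; no section states such a restriction. With prolonged abstainers as the denominator, 1b would mean that only 25% and 15% of self-reports are confirmed (0.25 × 14% = 3.5% and 0.15 × 7% = 1.05% of all participants), which is not how 1b is worded.

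**Step 5: power, if 1b were restated as verified prolonged abstinence.** Same layout, with equal confirmation in both conditions (assumed):

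| Confirmed | Rates | Power |
|---|---|---|
| 100% | 14% vs 7% | 0.806 |
| 90% | 12.6% vs 6.3% | 0.759 |
| 80% | 11.2% vs 5.6% | 0.703 |
| 70% | 9.8% vs 4.9% | 0.640 |
| 50% | 7% vs 3.5% | 0.490 |

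The layout gives 0.872 for 25% vs 15%. Six periods of 40 would give 0.694 for 14% vs 7% and 0.771 for 25% vs 15%.

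**Step 6: extra tests, if all 7-day abstainers are tested.** Assume even recruitment and complete follow-up.

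- By start times, control recruits = 3 sites × (6 + 13 + 19) months × 40/6 = 760, leaving 1400 in the intervention condition. Extra tests ≥ 0.11 × 1400 + 0.08 × 760 = 154 + 61 = 215.
- With the 6-month offset, control = 3 × (12 + 19 + 25) × 40/6 = 1120, leaving 1040. Extra tests ≥ 0.11 × 1040 + 0.08 × 1120 = 114 + 90 = 204.

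Both are floors: they count expected passes, and those who fail are also tested.

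**The case against.** The best defence is grammatical. The comma before the last clause could let the Smoking section name two groups: those reporting prolonged abstinence, and those reporting no smoking in the last week. That would reconcile it with 1b and with both tables. It is not the natural reading, and if it was intended the sentence still needs rewriting, because site staff could follow the literal version.

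The tables are sometimes read as naming a different test population. They do not: they leave the type of abstinence open. They therefore permit testing all 7-day abstainers without requiring it, and do not override the outcome definition.

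Three stronger inferences should be resisted.

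- **That the difference is capped at 7 points, so a 10-point effect is unattainable.** A ceiling on each rate does not cap their difference. If all intervention reports but only 57% of control reports were confirmed, the rates would be 14% and 0.57 × 7% = 4%, a gap of 10 points. Only the levels 25% and 15% are excluded.
- **That 14% and 7% limit what will be observed.** They are hypothesised rates. The incompatibility is between the protocol's own planning figures and its definition.
- **That late quitters will be counted as unverified.** The article does not say how untested participants are coded, and that commonly belongs to the analysis plan.

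**Conclusion.** The point holds. On the plain reading of the Smoking section, and with the same participants as denominator in 1a and 1b, the verified levels in 1b exceed what the definition allows by factors of 1.79 and 2.14. The outcome named in 1b and the outcome the protocol sets out to measure are not the same.

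Its weight is moderate. The primary outcome is self-reported prolonged abstinence, its power claim reproduces under the assumed layout, and neither depends on the testing rule. A reader might treat the problem as fatal because 1b stands under Primary hypotheses. The outcome sections list verified abstinence as secondary, however, and the main sample-size justification is untouched. It is best corrected before 7-month data collection, since untaken samples cannot be replaced.

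**What to change.** Reword the Smoking section so that every participant who reports no smoking in the past 7 days at the 7-month interview is offered the test, whether or not prolonged abstinence is reported. Define 1b as that self-report plus a passed test, report verified prolonged abstinence as a separate outcome, and have Tables 1 and 2 name the same test population.

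If the sponsor instead intends verified prolonged abstinence, restate 1b in those terms with rates no higher than 14% and 7%, say so in both tables, and recheck its power under stated confirmation rates. The choice is the sponsor's.

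The first repair costs an amendment and more uses of a test already in the schedule: at least about 200 at the hypothesised rates, and more once failed tests are counted. The second adds no tests, but 1b then rests on lower rates and probably on less power.

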### Sample size

The trial will recruit 2160 smokers (40 per site per 6 months over 3 years for each of nine sites). This sample size will provide approximately 80% power to detect a difference of 7% in smoking cessation (i.e. during the baseline phase 7% of those who were smokers or recent quitters at recruitment will achieve 6 months prolonged abstinence, while during the intervention phase 14% of those who are still smoking at diagnosis will achieve 6 months abstinence) at an alpha level of 0.05, assuming an intra-cluster correlation of 0.01 and a worst-case scenario of cluster autocorrelation equal to zero. This sample also provides over 90% power to detect each of the differences previously stated for the secondary outcomes.

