### Evaluation

#### Statistical methods

Independent and blinded statisticians from the CReDITSS Unit at the Hunter Medical Research Institute, Australia, supervised by CI [name], will conduct analyses of the primary and secondary outcomes.

Logistic regression within a generalised linear mixed models framework will be used to model the primary and secondary outcome measures. All models will adjust for time using a fixed effect that describes the phase of the study (pre-intervention and each of the 3 steps). Variation between sites will be accounted for using a random effect for site and repeated measures on sites will be accounted for using a random effect for time within site. To estimate the intervention effect, a variable indicating when the intervention was active for a given site and time will be included in the models. As the timing of the 7 month CATI for some participants overlaps with intervention commencement, the analyses of 6 months abstinence will include a 6-month offset to the coding of the intervention indicator variable to allow the full effect of the intervention to be in place before estimating its effect.

There are no plans for interim analyses.

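### The nicotine-dependence outcome cuts a 0–6 score into three bands, which discards information that is already collected; a minor and cheap improvement.

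*Protocol article*

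**What the plan says.** Under Secondary outcomes (Smoking), nicotine dependence is assessed with the two-item HSI: "It uses a six-point scale calculated from the number of cigarettes smoked per day" and the time to the first cigarette after waking, each in four categories. The score is then banded: "Nicotine dependence is then categorized into a three-category variable: low (0–1), medium (2–4) and high (5–6". The bands run from 0 to 6, so there are seven possible values, and the middle band holds three of them.

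The same list keeps one of the two items as an outcome of its own: "Daily consumption: cigarettes per day (CPD) as measured by item 1 of the HSI". Length of quit attempts is also listed.

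The Statistical methods section has one model statement for all outcomes: "Logistic regression within a generalised linear mixed models framework will be used to model the primary and secondary outcome measures". It names no ordinal, multinomial or linear variant. Nicotine dependence appears in neither the Primary nor the Secondary hypotheses, and the Sample size section gives it no effect size and no power.

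**The concern.** The two items already yield an ordered score for every patient who answers them. Defining the outcome as three bands discards all differences within a band before any model is fitted. The largest loss is in the middle, where scores 2, 3 and 4 become identical. This holds for whichever patients have a score, and it holds even if the three levels are modelled correctly as ordinal.

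At stake is the precision of one secondary comparison. If the intervention shifts the distribution of dependence at 7 months, the banded analysis needs a larger shift, or more patients, to show it. The banding is a stated definition, not a detail left open, so it is fair to comment on it from the article alone.

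**Working it through.** **1. Reproduce the plan's own power figure, to fix the design.** Inputs from Sample size: "The trial will recruit 2160 smokers (40 per site per 6 months over 3 years for each of nine sites"; 7% versus 14%; "at an alpha level of 0.05, assuming an intra-cluster correlation of 0.01 and a worst-case scenario of cluster autocorrelation equal to zero". Statistical methods gives four phases. I assume a two-sided test and equal phases, so 2160/(9 × 4) = 60 patients per site-period.

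With cluster autocorrelation zero, site-period means are independent. The variance of the intervention effect is then the cell variance divided by Σ 9·x(1 − x), where x is the share of sites on intervention in each period. With x = 0, 1/3, 2/3 and 1, the sum is 0 + 2 + 2 + 0 = 4.

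- Cell variance = 0.105 × 0.895 × (0.01 + 0.99/60) = 0.00249
- SE = √(0.00249/4) = 0.02495
- Power = Φ(0.07/0.02495 − 1.96) = Φ(0.845) = 80.1%

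This matches "This sample size will provide approximately 80% power to detect a difference of 7% in smoking cessation". Other layouts give less: 68.8% for six 6-month periods with sites switching after the first, second and third, and 71.2% for uneven phases switching at 6, 13 and 19 months. I use the layout that matches the stated figure.

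**2. Patient-level efficiency of the bands.** Under proportional odds the information is proportional to 1 − Σp³, where p are the category probabilities. The article gives no HSI distribution, so the four below are assumptions.

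| Assumed % at scores 0–6 | Low/medium/high % | 1 − Σp³, seven values | 1 − Σp³, three bands | Efficiency |
|---|---|---|---|---|
| Mid-centred: 15/12/18/25/18/8/4 | 27/61/12 | 0.967 | 0.752 | 0.78 |
| Heavier: 6/8/15/25/25/14/7 | 14/65/21 | 0.962 | 0.713 | 0.74 |
| Lighter: 30/15/17/20/11/5/2 | 45/48/7 | 0.955 | 0.798 | 0.84 |
| All equal | 29/43/29 | 0.980 | 0.875 | 0.89 |

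**3. Translate to power in this design.** Assume 48 scored patients per site-period (80% of 60) and ICC 0.01 on the latent scale.

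- τ² = (π²/3) × 0.01/0.99 = 0.0332
- Cell variance of the log odds = 3/(48(1 − Σp³)) + τ²
- SE = √(cell variance/4); power = Φ(ln OR/SE − 1.96)

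Mid-centred case, three bands: 3/(48 × 0.752) + 0.0332 = 0.1164, SE 0.1706. Seven values: 3/(48 × 0.967) + 0.0332 = 0.0979, SE 0.1564. At OR 1.5 (ln 1.5 = 0.405), power is 66.2% and 73.6%.

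| Distribution | OR 1.2: bands → full | OR 1.5: bands → full | OR 2.0: bands → full |
|---|---|---|---|
| Mid-centred | 18.6 → 21.4 | 66.2 → 73.6 | 98.2 → 99.3 |
| Heavier | 18.1 → 21.3 | 64.5 → 73.5 | 97.9 → 99.3 |
| Lighter | 19.3 → 21.2 | 68.0 → 73.3 | 98.6 → 99.3 |
| All equal | 20.2 → 21.5 | 70.8 → 74.0 | 99.0 → 99.4 |

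The loss is 1.3–3.2 points at OR 1.2, 3.2–9.0 at 1.5 and 0.4–1.4 at 2.0.

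**4. Sensitivity.** A separate set of seven assumed distributions, using both the proportional-odds criterion and a linear score, gave efficiencies of 0.80–0.89 in six. The seventh, peaked with 70% of patients in the medium band, gave 0.68–0.78. If the full score had 80% power and clustering were ignored, the loss would be 4.6–9.5 points in the six and 10.5–16.2 in the peaked case. Every distribution tried showed a loss; only its size moves.

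**The case against.** **The size is not a property of this plan.** A reader might take a loss of several power points as a fact about the trial. The article does not support that: the score distribution, the effect and the number scored are all assumed. The loss is largest near OR 1.5, where the power curve is steep, and small at 1.2 and 2.0. This objection stands, so the figures above are illustrations only.

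**No patient is classed as changed or unchanged.** It is tempting to say that a smoker who falls from 4 to 2 counts as unchanged while one who falls from 2 to 1 counts as improved. The article defines no change score. Secondary outcomes are assessed at 7 months and compared across site-periods through an intervention indicator. The loss is in resolving follow-up scores, not in misclassifying individual change.

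**Partial benefit has other measures.** A reader might infer that banding removes the main way to see benefit short of quitting. Cigarettes per day and length of quit attempts are separate outcomes and are not put into these bands. Neither recovers time to first cigarette, so they mitigate the loss without fully replacing the score.

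**The logistic model does not prove a further cut.** Reducing the bands to two levels could cost about 11–41 points (80% reference power, no clustering), but the article does not say this will be done. The exact model is a matter for an analysis plan that is not shown.

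**The bands may have a source, and the full score may be analysed elsewhere.** The index is cited to a reference that cannot be checked here, and an unseen analysis plan could add the raw score. That is possible, but the published definition states the banding and nothing else.

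**Patients who quit have no natural score.** The lowest cigarette category starts at 1, so who is scored is a separate question that the intervention may affect. Using the full score does not resolve it.

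**Conclusion.** The point holds as a minor one. The article fixes a three-band outcome where a seven-value score is already available, gives no reason, and states no analysis of the full score. The direction of the loss follows from the pooling. Its size rests on assumed distributions and proportional odds: 74–89% of patient-level efficiency retained in the four main cases, and as little as 68% if scores bunch in the middle. The power figures rest further on four equal periods, 48 scored patients per site-period, ICC 0.01, zero cluster autocorrelation and a two-sided 5% test.

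Nothing here is invalid or contradictory. The primary outcome, the sample size and the stated hypotheses are unaffected.

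**What to change.** In Secondary outcomes (Smoking), define the analysed nicotine-dependence outcome as the 0–6 HSI score at 7 months. Analyse it with an ordinal (proportional-odds) or linear mixed model, keeping the time, site and intervention terms given under Statistical methods. Keep low, medium and high for descriptive tables. In the same edit, reconcile the description of the scale as six-point with bands that span seven values.

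The cost is a sentence or two in the outcome definition and the matching line in the analysis plan. Both items are already collected at baseline and 7 months (Table 2), so no new data or patients are needed. The small downside is that the effect is reported as a common odds ratio or a mean score difference instead of a shift between named classes.
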